**Figure 1 Fig1:**
[figure not shown]
**Summary flow chart for IPC-PLUS trial.** IPC = Indwelling pleural catheter, WHO/ECOG = World Health Organisation/Eastern Cooperative Oncology Group, PS = Performance status, CXR = Chest X-ray, CT = Computed tomography, VAS = Visual analogue scale, SOB = Shortness of breath, USS = Ultrasound scan.

### Pre-randomisation

Following consent, a baseline assessment will be undertaken by a member of the trial team and entered onto the appropriate case report form (CRF). This will include:Relevant medical history and physical examination, to include the onset and nature of symptoms, type of malignancy causing effusion (if known), pleural procedures to date, current ECOG/WHO performance status, current analgesia history and current and projected treatment plan outside of IPC-PLUS;Results of standard blood tests (from within 24 hours);Visual-Analogue Scale (VAS) score to assess thoracic pain and breathlessness;Quality of life assessment using EuroQol 5D (EQ-5D) and Quality of Life Questionnaire C30 (QLQ-C30) health questionnaires;Chest X-ray, ideally posterior-anterior (from within previous 10 days) andThoracic ultrasound scan.

Patients will then be given an appointment, if this has not already been provided, to have an IPC (PleurX® catheter, CareFusion, IL, USA) inserted as a day case procedure within one week of the baseline assessment.

IPCs must be placed by an appropriately trained member of staff, but not necessarily a member of the trial team. Immediately following drain placement, a therapeutic aspiration should be performed. During drainage, patients should have pleural pressures measured after every 100 to 200 mls of fluid removed, using a calibrated electronic pleural manometer (Mirador Biomedical, Seattle, WA, USA). Pressure measurements should be recorded along with the total volume removed. A chest X-ray should be performed post-procedure to confirm adequate drain placement.

Prior to discharge, the patient will be issued with a drainage booklet which will act as a record for the volumes of fluid drained throughout their period of trial participation. They will also be given a chart on which they can complete their own VAS scores for pain and breathlessness, which should be done on a daily basis.

For the period post IPC insertion and before their randomisation visit, patients should have their fluid drained on at least five occasions, the initial drainage being immediately after IPC insertion prior to discharge. This first drainage may be to the maximum clinically appropriate volume, with subsequent drainages to a maximum of 1,000 mls per drainage. The patient’s fifth drainage can take place as part of their randomisation visit.

Patients will attend their local trial centre 10 days (+/− one day, as above) after IPC insertion. Their pleural space should be drained to dryness, or as close to dryness as allowed by symptoms. Following this, they should undergo a chest X-ray (ideally posterior-anterior) and have an appointment with a member of the trial team, who will perform a standardised medical assessment. Quality of life will be assessed using the EQ-5D and QLQ-C30 questionnaires. The chest X-ray should be examined for evidence of lung entrapment and significant fluid. A thoracic ultrasound of the side where the IPC has been inserted should be performed, looking for evidence of fluid loculation and septation.

If there is evidence of significant lung entrapment (defined as >25% of the hemithorax without expanded lung visible on a chest X-ray, as judged by two separate clinicians) or significant pleural fluid (defined as pleural fluid, confirmed on thoracic ultrasound, occupying more than one third of the hemithorax as judged by two separate clinicians using visual estimation on a chest X-ray), then the patient should be excluded from randomisation. Patients who do not meet the criteria for randomisation should have their on-going care devolved to the appropriate local services. Patients may also be excluded for other clinical reasons not relating to the degree of lung entrapment or residual fluid. If a patient is eligible for trial continuation at this point then they should be randomised at the same visit and given the allocated treatment substance before returning home.

### Randomisation, blinding and emergency unblinding

Those who are eligible for will be randomly assigned in a 1:1 ratio to either receive intrapleural talc slurry (4 g Novatech Steritalc mixed with 50 mls 0.9% saline) via the IPC, or to receive a placebo instillation of 0.9% sterile saline alone.

Treatment allocation will be performed by an independent computer randomisation service, which will be accessed by the main trial coordination centre on behalf of recruitment centres following confirmation of suitability for randomisation. Minimisation with a random component will be used [19].

The minimisation factors are:Volume of pleural fluid removed in the first 10 days post IPC (≤1,999 mls or ≥2,000 mls),Malignancy subtype (ovarian and breast, mesothelioma or other), andDay 10 chest X-ray appearance (expanded with no evidence of trapped lung or evidence of trapped lung but fits the criteria for randomisation).

The study is to be performed in a single blind fashion. Patients are to be kept unaware of their treatment allocation, but the physician and other healthcare professionals involved with administering the slurry or placebo are made aware of the allocation. A number of methods are to be used to reduce the likelihood of a patient learning of their allocation. These include:Making the randomisation phone call in a separate room to the patient,Preparing the slurry or placebo in a separate room to the patient and ensuring materials are covered before the patient is brought in,Opaque syringes being used to make it less clear which substance is being administered andThe slurry or placebo being administered from behind the patient, with the patient facing forward.

Patients may have their treatment allocation revealed (unblinded) at any time according to clinical need. A 24-hour telephone number will be available for unblinding queries.

### Post-randomisation

The administration of the randomised substance should be followed by an adequate flush to ensure as little as possible is left in the IPC line. Patients should then be observed for a minimum of two hours before being discharged home. Observations should include at least half-hourly measurements of pulse, blood pressure, temperature, pain score and respiratory rate. Patients must have their first post-randomisation drainage between 12 and 36 hours after instillation, and early communication with community nursing teams is vital to ensure this takes place.

### Community drainage

Following randomisation, all patients should receive fluid drainage in the community, although if necessary patients may attend their local trial centre. Drainages will be done by an appropriately trained healthcare professional up to and including the day 28 follow-up visit. After this, until the end of the trial follow-up period, drainages may be performed by anyone with an appropriate level of training. This may include the patient’s family or carers, but should not be the patient themselves. The frequency of drainage will be at the discretion of the patient and community team, but should occur at least twice per week, and should begin at three times per week. Drainage volumes will be recorded on each occasion.

### Clinical assessments (days 14, 28, 42, 56 and 70 post-randomisation)

The follow-up period for each patient is 10 weeks post-randomisation, or until death. During this time, the first clinical assessment will occur 14 days after randomisation, and at two-weekly intervals thereafter. The appointments scheduled for days 42 and 56 may take place over the telephone. Appointments on days 14, 28 and 70 must take place at the base hospital or satellite centre.

### Face-to-face appointments (mandatory on days 14, 28 and 70, optional on days 42 and 56)

Before each assessment, but following arrival at the trial centre, the patient’s IPC should be drained to dryness by a trained member of staff. Patients should also have a chest X-ray (ideally posterior-anterior) after they are drained. The assessment should then be completed and will include:A record of any contact with medical services including hospital admissions and length of stay, outpatient care visit, emergency care visit and ambulance service use Complications of IPC placement through history and examination;Documentation of analgesia requirements (day 14 only);Documentation of chemotherapy and/or radiotherapy and any response;Current ECOG/WHO performance status;Quality of life assessments using EQ-5D and QLQ-C30 health questionnaires andA thoracic ultrasound scan, alongside completing the ultrasound CRF.

### Telephone appointments (optional on days 42 and 56)

Any appointment which is to be performed over the telephone should consist of the following:A verbal reminder to the patient to complete and send their quality of life questionnaires and VAS booklets back to their local trial centre, ensuring that a VAS score is completed during the telephone consultation.Completion of a specific telephone follow-up CRF by the researcher, along with the standard health service use CRF.A review of drainage volumes with the patient over the telephone.

If drainage volumes appear to have reduced to a level suggesting pleurodesis, or if there is any suspicion of a drainage or IPC complication, then the patient must attend for the next scheduled follow-up visit. Alternatively, a patient may attend the following day for a full face-to-face visit, with the telephone follow-up being discarded.

### Removal of drains

Once inserted, drains may be removed at any time at the clinical discretion of the patient’s primary physician, at the request of the patient or at the discretion of the trial team. If a drain is to be removed, patients should be given an appointment to have this done within 14 days of the clinical assessment at which this decision was taken. Any patient who has a drain removed during their post-randomisation trial period will continue to undergo planned follow-up for the full 70 days.

### Blockage of drains

All care should be taken to ensure IPCs do not become blocked, beginning with an adequate flush at the end of sclerosant administration. If there is a suspicion that a blockage has occurred then standard local unblocking procedures should be followed.

### Biological samples and storage

During the trial baseline assessment, all patients should have standard blood tests for full blood count, urea and electrolytes, liver function, clotting function and C-reactive protein taken if there are no results available from within the previous 24 hours. In addition to these, at the research sites at North Bristol and Oxford, one ethylenediaminetetraacetic acid (EDTA), one serum gel tube and one citrate tube of blood should be taken. During IPC insertion, one EDTA, one serum gel tube and one citrate sample tube of pleural fluid should also be collected from patients at the North Bristol and Oxford sites. All such trial samples should be processed and stored as per the appropriate standard operating procedure.

At the North Bristol and Oxford research sites, prior to each trial follow-up appointment (every two weeks for 10 weeks), additional samples of pleural fluid should be collected during IPC drainage, before being processed and stored in the same manner as above.

Participants will give their permission for linked anonymous blood and pleural samples to be stored and analysed at North Bristol NHS Trust (NBT), or, if from another site, for those samples to be transferred to NBT for storage and analysis. Samples will be stored in a dedicated freezer in the University of Bristol laboratory on the NBT site. Samples will be stored, anonymised and eventually destroyed in line with local policy.

### Ultrasound scans

All ultrasound scans must be performed by fully trained operators (with sufficient experience to scan and interpret images independently) on the local research team. Scans will be used to assess the presence and degree of pleural fluid complexity, and fluid depth.

### Visual Analogue Scale scoring

All patients will complete a VAS assessment of thoracic pain and breathlessness during their baseline assessment. After IPC insertion, beginning the following morning, patients should repeat this assessment using the documentation provided. VAS scores should then be recorded on a daily basis for the duration of trial involvement, with recordings being made each morning. If IPC drainage is due to take place that day, then the score should be noted before the drainage takes place.

### End of trial

The trial will cease recruitment once the target of 154 randomised patients has been met, or if the Trial Steering Committee feels the interim analysis after 100 patients justifies early cessation. The provisional end of trial date will therefore be 10 weeks after the randomisation of the final trial patient. At the end of each patient’s follow-up period they will be stratified as ‘alive’ or ‘dead’, and survival data collated. Further information regarding participants’ health status and survival may be obtained by accessing the NHS central register. This will require consent to be given separate to trial involvement. Those who still have an IPC *in situ* will have their care devolved to the appropriate local services.

### Patient withdrawal and loss to follow-up

Patients will have originally consented to trial follow-up procedures, including sample collection, storage and analysis where appropriate. Patients have the right to withdraw from the trial at any point. A request by a patient to withdrawal does not have to be justified and will not affect future or on-going care. In the event of withdrawal, any details available regarding the reason(s) should be recorded in the patient’s CRF. Patients may still be stratified as ‘alive’ or ‘dead’ at the end of their follow-up period, unless consent for clinical data use is withdrawn. Patients who withdraw before randomisation will not be included in the final analysis.

If a patient moves to an area outside of the trial centre catchment, every effort should be made to continue follow-up in conjunction with the new local services, or via the new GP. If this cannot be done, the patient will be recorded as ‘lost to follow-up’.

### Data collection and statistical considerations

#### Data collection

Data will be collected according to the schedule described above and in Table 2. Sites will enter data onto CRFs, which will be checked by the trial coordination centre before being entered onto an electronic database.

**Table 2 Tab2:** **List of major protocol amendments**

SA01	• Clarification of randomisation target of 154 patients
	• All references to Short Form 36 Quality of Life (SF-36 QoL) questionnaire removed
	• Added an exclusion criterion: patients must have access to phone for investigator trial contact
	• Clarified sample collection and analysis
	• Clarified procedure pre-randomisation
	• Clarified that patients may also be excluded from randomisation for clinical reasons other than X-ray appearances
	• Updated summary tables and clarified pre-randomisation day nomenclature
	• Stipulated a time window in which patients must have first indwelling pleural catheter (IPC) drainage post-randomisation
	• Clarified time window in which patients may have follow-up appointments
	• Clarified wording in safety reporting section and highlighted expected minor side effects from talc
	• Updated members of the Trial Steering Committee
	• New sites added: Preston, Portsmouth and Bristol Royal Infirmary
SA02	• Change of principal investigator at Portsmouth site
SA03	• New sites added: Worcester, North Staffordshire, North Tyneside, Middlesbrough, South Manchester and Blackpool
	• Creation of letter and short trial summary for district nurses
	• Alteration to primary endpoint; changing minimal fluid volume required for pleurodesis from 20 to 50 mls
	• Change to time limit given to patients to consider patient information sheet
	• Removed requirement that trial chest X-ray must only be taken as a posterior-anterior image
	• Trial flow chart updated, allowed patients to have follow-up appointments at satellite centres
	• Allowance for patients to be approached as an inpatient but management must be as an outpatient for trial
	• Clarifications to adverse event and serious adverse event reporting procedures
SA04	• New site added: Bath
SA05	• New sites added: London, Mansfield, Stockton-on-Tees and Sheffield
	• Clarification of wording of primary endpoint, removal of duplicate secondary endpoint and addition of new secondary endpoint
	• Clarification of definition of trapped lung in trial flow chart and protocol
	• Addition of new QoL questionnaire (QLQ-C30) for all new trial participants
	• Expanded the use of pleural manometry to all centres
	• Removed the need for 0.9% saline placebo to be sourced from a particular manufacturer
	• Updated wording of how the primary outcome will be analysed
	• Updated membership of the Trial Steering Committee
SA06	• New sites added: Northampton, Ayr, Cambridge, Aintree and Hull
	• Change of inclusion criteria to require World Health Organisation (WHO) performance of two or better to be eligible, three if score will decrease to two after drainage.
	• Allow patients with previous pleurodesis as long as longer than 56 days before trial entry
	• Relax follow-up visits by allowing day 42 and 56 to be carried out over the telephone
	• Allow carers or relatives to perform chest drains after the day 28 post-randomisation visit
	• Extend recruitment period to May 2015
	• Relaxation of manometry recordings from every 100 ml to every 100 to 200 ml
	• Updated membership of the Trial Steering Committee

The following CRFs will be used during the trial: enrolment, baseline assessment, IPC insertion, day 10 assessment and randomisation, follow-up, telephone follow-up, thoracic ultrasound appearances, health resource utilisation and withdrawal.

In addition to the above, patient data will also be collected via a daily patient VAS score booklet and a daily IPC drainage volume booklet.

#### Primary endpoint

The primary endpoint is the number of patients with successful pleurodesis at 5 weeks post-randomisation. For the primary outcome measure, successful pleurodesis will be defined as the collection of less than, or equal to, 50 mls of pleural fluid on three consecutive occasions, with chest opacification on the side of the IPC less than 25%, as judged by two independent clinicians, who should be blind to treatment allocation. Information on drainage volumes will be collected in the community and during follow-up visits as described above. The X-ray for chest opacification must have been taken after the third consecutive occasion of collection of less than 50 mls of fluid, and within the 10-week follow-up period. All three occasions of collection of less than 50 mls of fluid should also occur within the 10-week follow-up period.

Patients who drain less than 50 mls of fluid on three or more occasions but who continue to have greater than 25% pleural opacification on a chest X-ray due to pleural fluid (as proven by thoracic ultrasound), will be defined as having an unsuccessful pleurodesis. If there is a clinical suspicion that the drain may be blocked then appropriate attempts to resolve this should be made prior to a definition being made.

The achievement of pleurodesis should be dated to the first drainage of less than or equal to 50 mls. Even if patients achieve the requirements for pleurodesis during the trial period, they will continue to receive fortnightly follow-up visits as originally planned until the 70-day follow-up period is complete.

Patients who die during the 10-week trial period will be assessed for whether they achieved pleurodesis success prior to death. This requires the collection of less than, or equal to, 50 mls of pleural fluid on three consecutive occasions, with chest opacification on the side of the IPC less than 25%, as judged by two independent clinicians, who should be blind to treatment allocation, with the X-ray having been taken after the third consecutive collection volume of less than 50 mls.

#### Secondary endpoints

The secondary endpoints for this trial are as follows:Self-reported quality of life status, measured at 14, 28, 42, 56 and 70 days, using the EQ-5D and QLQ-C30 health questionnaires.Self-reported VAS scores, measured daily from randomisation to 10 weeks post-randomisation, for thoracic pain and breathlessness.Total volume of pleural fluid drained from randomisation to 10 weeks post-randomisation.All-cause mortality up to 10 weeks post-randomisation.Number of hospital inpatient bed-days required from randomisation to 10 weeks post-randomisation.Degree of loculation of pleural fluid following talc instillation as judged by thoracic ultrasound and septation score at two-weekly intervals for the 10-week follow-up period.Pleurodesis success at 10 weeks post-randomisation, as defined by consecutive fluid volume measurement.Number of pleural procedures to relieve pleural fluid, excluding IPC drainage, from randomisation to up to 10 weeks.Pleurodesis success at five and 10 weeks post-randomisation, as defined by total volume of fluid collected over two consecutive weeks.

As part of a secondary analysis, patients who have recorded drainages of less than or equal to a total of 250 mls of fluid over two consecutive weeks during their follow-up period (with appropriate radiological findings) will also be defined as having a successful pleurodesis. The period of two consecutive weeks may begin with any drainage which is undertaken during the post-randomisation trial period, and ends two weeks later on the same day of the week. The drainage volume recorded on this final day is included in the total volume for the two-week period. Patients must be drained no less frequently than twice per week.

In order to be defined as having a successful pleurodesis, a patient’s chest X-ray must have chest opacification on the side of the IPC of less than 25%, as judged by two independent clinicians, who should be blind to treatment allocation. The X-ray for chest opacification must have been taken after the last drainage of the two-week period, and within the overall 10-week follow-up period.

For patients who successfully drain less than or equal to 250 mls of fluid in a two-week period, the date of pleurodesis is defined as the day of the first drainage in that period. All drainages which count towards the total volume must occur within the study period.

Patients who die during the follow-up period will also be assessed for pleurodesis using measurements collected prior to death. The clinical and radiological parameters used to define successful pleurodesis by volume over time remain the same as those described above.

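### The secondary definition of pleurodesis (250 ml or less over two weeks) has no provision for a drain removed inside its window, so a primary success can be scored as a secondary failure

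*Protocol article*

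**What the plan says.** The Secondary endpoints section lists "Pleurodesis success at five and 10 weeks post-randomisation, as defined by total volume of fluid collected over two consecutive weeks". It then defines success as "recorded drainages of less than or equal to a total of 250 mls of fluid over two consecutive weeks during their follow-up period", with suitable radiology. The window "may begin with any drainage which is undertaken during the post-randomisation trial period, and ends two weeks later on the same day of the week". On the last day, "The drainage volume recorded on this final day is included in the total volume for the two-week period". The frequency condition is "Patients must be drained no less frequently than twice per week". The X-ray must follow the last drainage of the window and fall within the 10 weeks. The section also says how patients who die are assessed. It does not say how to classify a patient whose drain is removed inside the window.

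Under Removal of drains, "drains may be removed at any time at the clinical discretion" of the primary physician, and also at the patient's request or the trial team's discretion. Once removal is decided, "patients should be given an appointment to have this done within 14 days of the clinical assessment". Follow-up continues to day 70 after removal. The Background says that catheters are often taken out after a sustained fall in drained volume, and treats that fall as a surrogate for pleurodesis.

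The primary definition needs three consecutive drainages of 50 ml or less plus the X-ray criterion. It sets no minimum duration.

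**The concern.** A patient without a catheter cannot be drained twice a week. Once the drain is out, a window that is still open can no longer meet the frequency condition, however dry the pleural space is. The event that breaks the window is often a consequence of the outcome being measured. The same patient may therefore count as a success on the primary definition and a failure on this secondary one.

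At stake is the reading of one named secondary endpoint at five and 10 weeks. If removal for success is more frequent or quicker in the talc arm, more talc successes than control successes are lost and the contrast shrinks. A lower success rate on this endpoint would then partly reflect when drains were removed, not how much fluid formed.

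**Working it through.** The plan gives no figure for this endpoint. Its sample size of 154 belongs to the primary endpoint and is not in question. The check is a count of days, followed by an illustration on assumed losses.

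**Inputs**
- Window: opens on a drainage on day s and closes on day s+14; at least two drainages a week (Secondary endpoints).
- Primary drainage criterion: three consecutive drainages of 50 ml or less (Primary endpoint).
- Community drainage: starts at three a week, at least two a week (Community drainage).
- First drainage: 12 to 36 hours after instillation, so about day 1 (Post-randomisation).
- Visits: day 14, then every two weeks (Clinical assessments). Removal: 0 to 14 days after the deciding assessment, so 15 permitted days, or at any other time (Removal of drains).
- Planning rates: 60% and 85% (Sample size and power calculation).

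**Step 1: time to meet the primary drainage criterion.** At three a week, the drainages fall on about s, s+2 and s+4, which is 5 calendar days. At two a week, the third falls on about s+7, which is 8 calendar days.

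**Step 2: the exposed interval.** The secondary window closes on s+14. The gap is 14 − 4 = 10 days at three a week and 14 − 7 = 7 days at two a week. Removal in that gap leaves the window incomplete.

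**Step 3: removal decided at scheduled visits, three drainages a week.** Assume that no earlier drainage opens a qualifying window.

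| Low run starts (s) | Third low drainage (s+4) | First visit at which it is seen | Window closes (s+14) | Removal days that break it | Of 15 permitted days |
|---|---|---|---|---|---|
| 1 | 5 | 14 | 15 | 14 | 1 |
| 2 | 6 | 14 | 16 | 14–15 | 2 |
| 5 | 9 | 14 | 19 | 14–18 | 5 |
| 10 | 14 | 14 | 24 | 14–23 | 10 |
| 11–14 | 15–18 | 28 | 25–28 | none | 0 |
| 15 | 19 | 28 | 29 | 28 | 1 |
| 24 | 28 | 28 | 38 | 28–37 | 10 |

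The pattern repeats each fortnight. At two drainages a week, runs starting on days 1 to 7 have 1 to 7 failing days out of 15, and runs starting on days 8 to 14 have none. Unscheduled removal, which is allowed at any time, exposes any run shorter than 14 days.

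**Step 4: one patient.** Low volumes are recorded on days 10, 12 and 14, the day-14 X-ray meets the criterion, and the drain is removed at that visit. The primary criterion is met and dated to day 10. The secondary window would close on day 24, and nothing can be drained after day 14. Opening the window earlier does not help: the first drainage is at about day 1, so no window closes before day 15.

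**Step 5: illustration of size.** The loss fractions are assumptions, and the planning rates are borrowed from the primary endpoint. Without loss the difference is 85 − 60 = 25 points.
- 10% of successes lost in both arms: 0.60 × 0.90 = 54%, 0.85 × 0.90 = 76.5%; difference 22.5 points.
- 5% lost with IPC alone, 15% with talc: 0.60 × 0.95 = 57%, 0.85 × 0.85 = 72.3%; difference 15.3 points.
- 10% lost with IPC alone, 20% with talc: 54%, 0.85 × 0.80 = 68%; difference 14 points.
- The reverse of the second case, 15% with IPC alone and 5% with talc: 0.60 × 0.85 = 51%, 0.85 × 0.95 = 80.8%; difference 29.8 points.

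The result depends on which arm loses more, and the document gives no removal rates by arm.

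**The case against.** **A window may be complete, or nearly so, before removal.** Removal may come up to 14 days after the decision, and a window completed by then stays met. The window may also open with a drainage above 50 ml, because only the 250 ml total is limited. Both points stand: some of these patients will be lost, not all.

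**A lenient reading is possible.** If no drainage is needed on the final day and two drainages in each week suffice, a patient drained three times a week (s, s+2, s+4, s+7, s+9) satisfies the condition by s+9. The gap falls from 10 days to 9 − 4 = 5. That narrows the problem without closing it. The day-10 patient in the working still fails if the earlier drainages take any longer window over 250 ml.

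**The rule may add a route to success.** The text says that patients meeting the 250 ml rule will also be counted as successes, which could mean in addition to primary successes. The endpoint list, however, names a separate outcome defined by two-week volume, so the stand-alone reading is the better supported. The wording is ambiguous at best.

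**Such rules belong in the analysis plan.** A separate plan is announced and is not shown. But the article sets out this definition in full: start, end, final-day volume, frequency, X-ray timing, dating and death. Followed exactly, it produces the misclassification, so this is more than condensed detail.

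**Stronger readings that do not hold.** A reader might infer that the fastest successes are the ones lost. The table shows otherwise under visit-based removal: a run starting on day 1 fails only if the drain comes out on day 14, while one starting on day 10 fails on 10 of 15 permitted days. A reader might also take this endpoint to be the only check on the frequency-dependent primary definition. The same section lists total volume drained and further pleural procedures, and neither needs three consecutive low drainages.

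**Conclusion.** The point holds in a limited form. As written, the two-week definition and the removal section conflict for any patient whose drain is removed for success before day s+14, and such a patient can be a primary success and a secondary failure. The exposed interval is about 7 to 10 days after the primary drainage criterion is met, assuming the stated drainage frequencies and that the window must run to its last day.

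The risk is set by the time from the start of low volumes to removal. Bias towards no difference follows only if removal for success is more frequent or quicker with talc. That is plausible under the trial's hypothesis, and removal is discretionary while the staff administering treatment know the allocation, but the document does not establish it. A reader might want to attach a size. None can be derived, and the differences of 14 to 29.8 points in the illustration rest on assumed losses.

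The primary endpoint and the sample size are untouched. The consequence is confined to one secondary endpoint, and it is worth correcting because the correction is cheap.

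**What to change.** Reconcile the two sections with one classification rule, fixed before unblinding and leaving the removal policy as it is:

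- If the drain is removed inside the window after the primary drainage criterion has been met, days after removal count as zero volume and as satisfying the twice-weekly condition.
- This applies only if no further pleural procedure for fluid takes place and an X-ray at or after the end of the window, within the 10 weeks, shows less than 25% opacification.
- Report a sensitivity analysis using the definition as now written.
- In the same sentence or the next, say whether the two-week definition stands alone or adds to primary successes, and whether a drainage on the final day is required.

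The cost is a sentence or two. Further pleural procedures are already recorded to 10 weeks, follow-up continues to day 70 after removal, and X-rays are taken at the mandatory visits.

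There are three downsides. The rule assumes no hidden re-accumulation after removal, which the X-ray checks. For these patients the endpoint overlaps more with the primary definition. It also brings removal decisions into the outcome, and these may be made by clinicians who know the allocation. The sensitivity analysis shows how much the result depends on the rule.
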